**Figure 2. Data collection schedule.**

| Study Month:                                    | 0 | 1 | 2 | 3 | 4 | 5 | 6 | 7 | 8 | 9 | 10 | 11 | 12 |
|-------------------------------------------------|---|---|---|---|---|---|---|---|---|---|----|----|----|
| FULL SAMPLE (n = 2500)                   |   |   |   |   |   |   |   |   |   |   |    |    |    |
| Fecal samples                                   | X |   |   |   |   |   |   |   |   |   |    |    | X  |
| Randomized Rx                                   | X |   |   | X |   |   | X |   |   | X |    |    | X  |
| Capillary blood                     | X |   |   | X |   |   | X |   |   | X |    |    | X  |
| Appetite                                        | X |   |   | X |   |   | X |   |   | X |    |    | X  |
| MUAC                                            | X |   |   | X |   |   | X |   |   | X |    |    | X  |
| Mother's milk                       | X |   |   |   |   |   |   |   |   |   |    |    |    |
| IMMUNOLOGY SUBSAMPLE (n=750) |   |   |   |   |   |   |   |   |   |   |    |    |    |
| Mother's fecal                                  | X |   |   |   |   |   |   |   |   |   | X  |    |    |
| Venous blood                        | X |   |   |   |   |   |   |   |   |   | X  |    |    |
| Anthropometry                                   | X |   |   |   |   |   |   |   |   |   | X  |    |    |
| HemoQuant                           | X |   |   |   |   |   |   |   |   |   | X  |    |    |

1) Capillary blood sample for determination of hemoglobin and malaria parasite density.

2) Only collected from mothers of children 6-12 months old.

3) Data collected in subsamples are in addition to the data collected for the full sample.

4) Venous blood sample will be used for assays of cytokine secretion in response to antigenic stimulation (whole blood assay), acute phase proteins, immunoglobulins, and iron status indicators.

5) HemoQuant assay will be performed on fecal samples collected for parasitology; no additional samples will be collected.

### Justification Of Sample Size

Our starting point for the sample size calculation was the Immunology Subsample. The proposed starting sample size of about 750 children, after 15% attrition, provides 220 children per infection status group, randomly allocated into 2 treatment groups. Thus to compare treatment effects within infection groups, we plan to have about 110 children. Based on the ongoing work of Drs. [name], [name], and [name] in Nanjing China, where they are using the whole blood assay to assess cytokine responses to *Schistosoma mansoni*, 100 per group is a minimum number to detect important differences.

To generate this number of age-matched triplets for the Immunology Subsample, about 2500 children will need to be screened for infection. This will in fact be more than enough to address Aim 1. However, we propose to retain the entire group of 2500 children for several reasons. First, we want to retain the representative community-based sample to address Aim 1. The Immunology Subsample will be specifically constructed such that it is no longer representative of the community of young children. We want to make inference about the effects that would be observed if mebendazole treatment were provided to all young children in this environment, since screening for infection status would be impossible to implement in a public health program. Second, it has been our experience in Pemba that once community meetings have been held to inform and motivate participation in a research study, it is difficult to randomly select only some of the children into the actual study. Because participation in the study will confer some benefits to the study subjects and their communities, families resent being excluded from community-based studies. Third, the costs of implementing the Full Sample protocol are relatively small.

The sample size for the HemoQuant Subsample, 100 per infection intensity group, was based on our previous HemoQuant study of hookworm-related blood loss in Pemba school children. In that study we detected significant differences amongst infection intensity groups with 50 children per group, however, the spectrum of infection intensities in school children was much greater. Because infection intensities will be light in these young children, we have doubled our previous sample size to detect smaller blood losses.

The sample size for the metabolic studies was based on the high cost of isotopes and their analysis, and our previous experience conducting studies of this sort. Groups of 10 individuals are typical of most metabolic studies that use stable isotopes. The proposed sample size of 40 children will be large in the published literature; however, the heterogeneity of the children (with regard to nutritional status, malaria, and other recent infections) will be greater than most populations that have been studied.

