## Experimental Design and Methods

We propose to conduct a community-based individually randomized trial of 3-monthly mebendazole treatment to assess the outcomes described in the framework and aims. The study area will be a geographically contiguous group of villages selected for the convenience of sample transport to the laboratory (within about 30 minutes drive by landrover). The PHL is currently conducting a complete population census of Pemba Island, which will allow us to define an area large enough to generate the needed sample size.

A representative sample of 2500 children ages 6-23 months will be screened for helminth infection. All 2500 children will be randomly allocated to treatment with a 3-day course of mebendazole, 100 mg twice daily, or identical placebo. This regimen was chosen to replicate the same drug used in our preliminary trial, but to maximize the efficacy of this drug against hookworms and *T. trichiura*. The study period will be 12 months duration, so that children have their first and final assessments in the same calendar month of the year, thus holding constant any seasonal effects. Anemia and PEM (**Aim 1**) will be assessed in the full sample.

To answer **Aims 2 & 3**, age-matched triplets of children will be selected according to their infection status at baseline. A triplet will be comprised of two infected and one uninfected child of similar age. The two infected children will be matched for species of infection. 250 matched triplets (total n=750) will comprise the Immunology Subsample. We chose 2:1 matching of infected to uninfected, because we are dealing with 3 species of infection and we want to increase our capacity to examine differences by species. Based on our preliminary data, a starting sample of 2500 children will be required to generate at least 500 infected cases. These children will be assessed for immunological parameters at baseline (prior to treatment) and again in the 10th month of the study, one month after the 4th (9-month) treatment round. The post-treatment time was chosen to maximize treatment effect by capturing all 4 rounds of treatment and by timing the assessment one month after the final treatment, when egg counts should be maximally reduced by the mebendazole.

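### The Immunology Subsample's single figure of 220 per infection status group (about 110 per arm) contradicts the 2:1 triplet design, which leaves about 425 infected and 212 uninfected children

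*Protocol*

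**What the plan says.** Under Experimental Design and Methods, the protocol sets the composition of the subsample for Aims 2 and 3: "A triplet will be comprised of two infected and one uninfected child of similar age". It gives the total as well: "250 matched triplets (total n=750) will comprise the Immunology Subsample". The screening number is tied to the same count, since "a starting sample of 2500 children will be required to generate at least 500 infected cases". The reason for taking two infected children for each uninfected child is that "we are dealing with 3 species of infection and we want to increase our capacity to examine differences by species".

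Under Justification Of Sample Size, the starting number of about 750 is said, "after 15% attrition, provides 220 children per infection status group, randomly allocated into 2 treatment groups". The next sentence reads: "Thus to compare treatment effects within infection groups, we plan to have about 110 children". The adequacy criterion, taken from related work with the same assay, is that "100 per group is a minimum number to detect important differences". That section gives no number by species. It states no significance level, power, standard deviation or effect size for this subsample.

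**The concern.** The design section makes the infected group twice the size of the uninfected group. The sample-size section then gives one number for each infection status group, as if the two were equal. The protocol names this subsample as the starting point of its sample-size calculation, so the figure should follow from the design.

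What is at stake is mainly Aim 3, the effect of mebendazole on the immune response of infected children. A reader cannot tell whether that comparison is planned with about 110 or about 212 children per arm. The uninfected cell is also given as slightly larger than the design delivers.

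**Working it through.** **Inputs.** 250 triplets, two infected to one uninfected, 750 children in all (Experimental Design and Methods). Attrition of 15%, two treatment groups, stated results of 220 and about 110, and a minimum of 100 per group (Justification Of Sample Size). Equal allocation to the arms is implied by the step from 220 to 110.

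**Trying to reproduce 220.**
- Uninfected group, or one third of the sample: 250 × 0.85 = 212.5.
- Infected group: 500 × 0.85 = 425.
- Half of the sample: 750 × 0.85 / 2 = 318.8.
- Dividing by 1.15 in place of multiplying by 0.85: 250 / 1.15 = 217.4, and 217.4 / 2 = 108.7 per arm. This is the nearest match, but it is not a 15% loss, and it fits only a group of 250, never the infected group (500 / 1.15 = 434.8).
- Attrition implied by the stated figure: two groups of 220 make 440, and 1 − 440/750 = 41%. Three groups of 220 make 660, and 1 − 660/750 = 12%. Neither is 15%.

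**What the design gives after 15% attrition.**

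| Group | Start | After 15% loss | Per arm | Stated per group | Stated per arm |
|---|---|---|---|---|---|
| Infected | 500 | 425 | 212.5 | 220 | about 110 |
| Uninfected | 250 | 212.5 | 106.25 | 220 | about 110 |
| Total | 750 | 637.5 | | | |

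**Size of the discrepancy.** Infected: 220/425 = 0.52, so the group is understated by about half. Uninfected: 220 − 212.5 = 7.5 children (3.5%), or about 4 per arm. Against the minimum of 100, both cells pass (212 and 106 per arm).

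**Illustration of precision.** This assumes 80% power, a two-sided 5% level and an unadjusted two-sample comparison of means; the protocol states none of these for this subsample. The detectable difference is (1.96 + 0.842) × √(2/n) standard deviations, with n per arm: 0.38 at n = 110, 0.27 at n = 212.5, and 0.38 at n = 106.

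**Species, as a conditional calculation only.** The protocol gives no species distribution and no co-infection rate. A species with share s of the 425 infected completers has 425 × s / 2 per arm:

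| Share s | 10% | 20% | one third | 40% | 50% | 60% |
|---|---|---|---|---|---|---|
| Per arm | 21 | 43 | 71 | 85 | 106 | 128 |

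Reaching 100 per arm needs s = 200/425 = 47%. Three non-overlapping species groups at 100 per arm would need 3 × 200 = 600 infected completers against 425, so at least one would fall short. Not split by arm, equal thirds give 425/3 = about 142 per species.

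**The case against.** The strongest reply is that this is a slip without consequence. The only adequacy criterion in the text is 100 per group, and both true cells meet it. The uninfected figure is off by about 4 children per arm in a section that speaks of about 750 and about 110. The error for infected children is in the cautious direction. The figure of 220 does not drive the screening number either: 2500 is tied to finding 500 infected children, and 500 is exactly 2 × 250. All of this stands, and it limits the point to a misstatement. It does not remove it, because a factor of two in the infected group is not rounding.

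A reader might go further and infer that comparisons by species fall below the protocol's own minimum. The documents do not support that. The design section says only that "we want to increase our capacity to examine differences by species"; it sets no species target and makes no claim that such comparisons are adequately sized. The minimum of 100 follows directly on the treatment comparison within infection groups and is not applied to species. The 71 per arm depends on equal, non-overlapping thirds. With co-infection the groups overlap and a shortfall need not arise. Differences by species may also mean baseline comparisons not split by arm, where the same equal split gives numbers above 100.

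**Conclusion.** The figure is wrong as written. A single count of 220 per infection status group, with about 110 per arm, cannot follow from 250 triplets in a 2:1 ratio with 15% attrition. The counts that do follow are about 425 infected (212 per arm) and about 212 uninfected (106 per arm). This conclusion rests only on the protocol's own triplet composition and attrition rate, with equal allocation and the same attrition in both groups.

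The practical effect is modest. The infected comparison for Aim 3 is better supported than the text says, the uninfected comparison is marginally less so, and neither falls below the stated minimum. It would be wrong to infer that the subsample is too small or that recruitment must rise. The species calculation shows what would happen under an assumed split and is not evidence of a fault in the plan.

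**What to change.** In Justification Of Sample Size, replace 220 per infection status group and about 110 per arm with about 425 infected (about 212 per arm) and about 212 uninfected (about 106 per arm) after 15% attrition. The statement that each cell exceeds 100 can remain.

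Optionally, add a sentence giving the expected number per species and arm together with the species distribution and co-infection rate assumed. If equal, non-overlapping thirds are assumed, that number is about 71 per arm, and the text should then say that three separate species groups cannot all reach 100 per arm.

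The cost is one or two sentences. Recruitment, screening and the triplet design are unchanged.

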## 1. Study Protocol

### Aims Of The Project

**Aim 1:** To test whether community-based periodic treatment of children 6-23 months old with mebendazole will decrease rates of severe anemia and protein-energy malnutrition by at least 20%.

**Aim 2:** To determine whether young children infected with intestinal nematode infections exhibit a more pro-inflammatory response to nematode antigens (i.e. characteristic of T Helper 1 [Th1] cells) than age-matched uninfected children.

**Aim 3:** To test whether mebendazole treatment of infected children reverses this pro-inflammatory response.

**Aim 4:** To measure intestinal blood loss related to relatively light hookworm infection in young children, and whether intestinal blood loss is reduced after treatment with mebendazole.

**Aim 5:** To elucidate metabolic mechanisms that could explain the link between a pro-inflammatory cytokine response and anemia and protein-energy malnutrition. Specifically, we aim:

A) To determine whether newly infected children show defects in iron metabolism compared to age-matched uninfected children, in a manner consistent with mechanisms of the “anemia of chronic disease” (i.e. decreased iron absorption, decreased iron incorporation into erythrocytes, suppressed erythropoiesis, and/or shortened red cell life span);

B) To determine whether newly infected children catabolize protein at greater rates than age-matched uninfected children;

C) To determine whether newly infected children are more anorexic than age-matched uninfected children.

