To answer **Aim 4**, a subsample of 300 children will be constructed of hookworm-negative (n=100), light hookworm infections (1-999 epg, n=100) and moderate hookworm infections ( $\geq 1000$  epg, n=100). These classifications are lower than typically used in school children, and were chosen for children 6-24 month who have lighter infection intensities but whose total body iron store is limited or absent. Therefore small quantities of GI blood loss could have significantly alter their iron balance. Intestinal blood loss will be measured in this subsample at just prior to treatment, and 1 and 12 months post-treatment. This HemoQuant subsample will be drawn from the Immunology Subsample, so that immunologic data will also be available.

To answer **Aims 5A and 5B**, a subsample of 20 newly-infected and 20 uninfected (total n=40) children will be selected from the Immunology Subsample. This number, although small for an epidemiologic study, is large for a metabolic study involving stable isotopes. To our knowledge it is the largest sample size ever involved in a similar protocol. However, many factors may affect the metabolism of these children and it is essential to limit the heterogeneity within this sample to reduce variance unrelated to the factors of interest (i.e. helminth infection status and cytokine response). Thus, we will impose inclusion criteria based on age (12-23 months old), wasting malnutrition (weight-for-height Z scores  $\geq -1$ ), recent illness (no significant morbidity in the prior 2

weeks, and malaria infection (<1000 parasites/mL). Because these children will be drawn from the age-matched triplets defined for the Immunology study, the 20 children in the newly-infected group and the uninfected groups will be further matched on age within the 1-year-old age category.

**Specific Aim 5C** will be addressed using maternal reports of poor appetite, a method that is valid and very simple to implement. Therefore anorexia will be assessed in the full sample of 2500 children just prior to treatment and at 3, 6 and 12 months post-treatment.

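### The HemoQuant sample size is justified only for comparing hookworm intensity groups; Aim 4's treatment question has no stated size basis and would be better served by a pooled, baseline-adjusted comparison

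*Protocol*

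**What the plan says.** Aim 4 has two parts. One is to measure intestinal blood loss from relatively light hookworm infection. The other is "whether intestinal blood loss is reduced after treatment with mebendazole" (Aims Of The Project).

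The subsample for this aim has 300 children: "hookworm-negative (n=100), light hookworm infections (1-999 epg, n=100) and moderate hookworm infections", the last group also of 100 (Experimental Design and Methods). It is nested in a larger one: "This HemoQuant subsample will be drawn from the Immunology Subsample". Every child in the trial is randomised: "All 2500 children will be randomly allocated to treatment" with mebendazole or placebo.

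The section Justification Of Sample Size rests the 100 per group on a previous study in school children, where "we detected significant differences amongst infection intensity groups with 50 children per group". Expecting only light infections at this younger age, it then says: "we have doubled our previous sample size to detect smaller blood losses".

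For the Immunology Subsample, the same section deducts 15% attrition, arrives at 220 per infection status group, splits that between two treatment arms, and reports about 110 for treatment effects within infection groups. The HemoQuant paragraph takes neither step. Data Analysis says that Aims 2 to 5 will be analysed by comparing means between groups formed by pre-treatment infection status or by treatment arm.

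**The concern.** The reason given for 100 per group is a contrast among intensity groups. That contrast uses all 100 children in each group at baseline, and its rationale is at least stated. The treatment question uses the children differently, because randomisation divides each intensity group between two arms. The protocol does not say how many children per arm support this question, or whether it will be asked within each intensity group or across all infected children.

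The choice matters. Asked within one intensity group, the comparison has about as many children per arm as the previous study had per group, and this is the size the protocol doubled because infections here are light. Asked across all infected children, it has about twice as many. Study Limitations calls the randomised design the strongest tool of the study, so the randomised part of Aim 4 should not be left on an undefined footing. An imprecise null result within one intensity group could be misread as showing that treatment does not affect blood loss.

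**Working it through.** **Inputs from the protocol**
- 100 children per intensity group, in three groups (Experimental Design and Methods).
- 50 per group in the previous study (Justification Of Sample Size).
- 15% attrition, stated for the Immunology Subsample only.
- 1:1 allocation, implied by 220 per infection group giving about 110 per arm.

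**Assumptions (the protocol gives no such figures for HemoQuant)**
- Two-sided alpha of 0.05 and 80% power.
- Differences expressed in SD units.
- The 15% attrition carries over to this subsample.
- A correlation of r = 0.5 between baseline and follow-up fecal heme.

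**Step 1. The plan's own figure.** 2 x 50 = 100 per group, which reproduces exactly. No power calculation can be reproduced, since alpha, power, SD and effect size are not given.

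**Step 2. Children per arm**
- Within one intensity group: 100 / 2 = 50; with attrition, 50 x 0.85 = 42.5.
- Light and moderate pooled: 200 / 2 = 100; with attrition, 100 x 0.85 = 85.

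**Step 3. Smallest detectable difference.** Unadjusted: (1.96 + 0.842) x sqrt(2/n). With baseline adjustment, multiply by sqrt(1 - r^2) = sqrt(0.75) = 0.866.

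| Comparison | n per arm | Unadjusted (SD) | Adjusted, r = 0.5 (SD) |
|---|---|---|---|
| Within one intensity group, no attrition | 50 | 0.560 | 0.485 |
| Within one intensity group, 15% attrition | 42.5 | 0.608 | 0.527 |
| Light and moderate pooled, no attrition | 100 | 0.396 | 0.343 |
| Light and moderate pooled, 15% attrition | 85 | 0.430 | 0.372 |

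**Step 4. The same contrast as power.** An unadjusted effect of 0.396 SD, which 100 per arm detects with 80% power, has 51% power at 50 per arm, 45% at 42.5 and 73% at 85.

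**Step 5. Can adjustment alone make up the difference?** For 50 per arm to match the unadjusted precision of 100 per arm, 1 - r^2 must equal 50/100, so r = sqrt(0.5) = 0.71. From 42.5 per arm, r = sqrt(1 - 0.425) = 0.76. The protocol gives no correlation to compare with these.

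**The case against.** A reader might infer three stronger things, none of which the protocol supports.

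- **That the sample size is miscalculated.** It is not. Twice 50 is 100, and the section says plainly that the figure is per intensity group. It claims no power for the treatment comparison.
- **That 50 per group had been judged too small.** The protocol says that 50 per group did detect differences in school children, whose intensities covered a wider range. The doubling was a choice made for lighter infections.
- **That the trial would probably miss the treatment effect.** Without an SD or an expected effect, detectable differences in SD units cannot show this.

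The comparison within an intensity group is itself only one possible reading. Aim 4 does not ask for it, and Data Analysis says infection status or treatment arm, not one within the other. The wording about treatment effects within infection groups belongs to the Immunology Subsample. If the infected children are simply compared by arm, there are 100 per arm before attrition and the shortfall disappears. The 15% attrition is also borrowed, and loss by 1 month may be lower.

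Precision within an intensity group could also be better than the table shows. Experimental Design and Methods plans two post-treatment measurements. If they were averaged, with r = 0.5 among all three measurements, the variance factor would be (1 + 0.5)/2 - 0.25 = 0.5, and 50 per arm would reach 0.560 x 0.707 = 0.396 SD. The same averaging would bring the pooled comparison to 0.396 x 0.707 = 0.280 SD, so the advantage of pooling remains. It also depends on the follow-up times, which are not settled: the text gives 1 and 12 months, while Figure 2 shows HemoQuant at months 0 and 10 only.

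Finally, the model details could properly sit in a statistical analysis plan. That is fair for the details. But the size justification is in this document and leaves out half of the aim it serves, and the analysis it does name is a plain comparison of means.

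**Conclusion.** The point stands as a gap in the justification and an inexpensive gain in precision. The stated basis for 100 per group covers the comparison among intensity groups only, and the treatment half of Aim 4 has none.

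If treatment were compared within an intensity group, about 50 children per arm (about 42 with the borrowed attrition) would detect 0.56 to 0.61 SD unadjusted, or 0.49 to 0.53 SD adjusted. Pooling the infected children with the same adjustment gives 0.34 to 0.37 SD. With adjustment credited equally to both, the gain comes from pooling and is a factor of sqrt(2), so the detectable difference is about 29% smaller (1 - 1/sqrt(2) = 0.293). Moving from a plain comparison of means within an intensity group to the pooled, adjusted analysis combines both gains.

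The figures rest on the assumed alpha, power, attrition and correlation. The split of 100 into about 50 per arm needs only the implied 1:1 allocation. The baseline comparison among intensity groups is unaffected.

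**What to change.** - In Data Analysis, replace the plain comparison of means for Aim 4's treatment question with mebendazole versus placebo in all hookworm-infected children of the HemoQuant Subsample (light and moderate pooled). Analyse log fecal heme, adjusted for log baseline heme and baseline egg count. Make intensity-specific treatment effects secondary.
- In Justification Of Sample Size, say that the doubling concerns the comparison among intensity groups. Give the per-arm number for the treatment comparison: about 100, or 85 if 15% attrition is assumed to apply here too.
- Name the follow-up time for this analysis, after reconciling the HemoQuant times in Experimental Design and Methods with those in Figure 2.

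**Cost.** Wording only: no extra children or samples, since baseline fecal heme is already to be collected. The price is that the main result becomes an average effect over light and moderate infections, with effects in each intensity group reported as secondary and less precise. Keeping 100 per arm within every intensity group instead would need 200 children per group, or 200 / 0.85 = 235.3, so 236, with 15% attrition. That is more than double the planned subsample.
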